## Introduction

### Background and rationale {6a}

In the German healthcare context, optimizing diagnostic efficiency is essential due to increasing demand for prostate cancer screening and limited reimbursement for mpMRI. Although MRI-targeted pathways have demonstrated clinical effectiveness, evidence for their cost-effectiveness and scalability in Germany remains limited. PRIMA addresses this gap by evaluating a high-quality, quality-assured MRI pathway that could reduce unnecessary biopsies and downstream treatment costs while maintaining diagnostic accuracy. Prostate cancer (PCa) is the most common solid cancer among men in Germany, with around 75,000 new diagnoses and 15,000 deaths annually, representing 25% of new male malignancies [1]. Classical diagnostic algorithms combining PSA, DRE, and 12-core SB lead to both overdetection of indolent PCa and missed csPCa [2]. Overdiagnosis results in unnecessary treatment, side effects, and psychological burden, whereas underdetection may delay curative therapy. Several prospective studies have demonstrated that TB alone provides similar detection proportions of csPCa compared with SB, while significantly lowering detection of clinically insignificant cancers [3–7]. Nonetheless, other reports suggest that SB still adds incremental diagnostic value [8–13]. The absolute additional yield of SB for csPCa detection has been estimated at 4–5% in two randomized trials and a Cochrane review [8–10], while TB alone may reduce the detection of ISUP grade group 1 cancers by up to 40% [7]. More recent data from the PROBASE trial in younger men (45–55 years) in a screening setting demonstrated that SB identified 26% additional csPCa compared with TB alone, whereas TB contributed only 6% additional csPCa [14]. Screening trials such as STHLM3-MRI [11] and Göteborg-2 [12] provided population-level insights. In STHLM3-MRI, MRI-based pathways reduced unnecessary biopsies and detection of low-grade cancers but would have missed ~1.7 csPCa cases for each avoided ISUP 1 diagnosis [11]. Göteborg-2 demonstrated comparable csPCa detection between TB-only and combined strategies, with fewer insignificant cancers in the TB-only arm (0.6% vs 1.2%), though some intermediate-risk cancers were detected only by SB [12]. Together, these studies highlight that MRI-targeted pathways can safely reduce overtreatment but may risk missing a small proportion of csPCa. Within Germany, mpMRI before biopsy is guideline-recommended [15]. However, the routine addition of SB remains under debate. The PROBASE trial, focusing on younger men (45–55 years), revealed that SB detected 26% additional csPCa compared to TB, suggesting that MRI interpretation and tumor biology may differ with age [16]. Furthermore, the PRIME trial recently demonstrated that bpMRI could suffice in older men (median age 65) [17], whereas PRIMA intentionally uses mpMRI to address potential diagnostic challenges in younger and intermediate-risk groups [18, 19]. Beyond diagnostic accuracy, PRIMA integrates patient-reported outcomes (PROs) to assess procedural burden (VAS) and quality of life (EORTC-QLQ-C30, EPIC-26). These outcomes are essential as biopsy techniques evolve from transrectal to transperineal approaches, potentially reducing infection risk and improving patient experience [13]. Quality assurance (QA) is a major element of PRIMA: all radiology centers are Q2-certified, ensuring compliance with PI-RADS v2.1 [20] and PI-QUAL v2 [21] standards, while urologists must document proficiency in ≥ 100 fusion biopsies. Despite robust international data, most trials have mixed cohorts with prior biopsy history, different MRI protocols, or lacked uniform QA. PRIMA is unique in enrolling exclusively biopsy-naïve men with well-defined MRI risk thresholds (PI-RADS 4/5 or PI-RADS 3 with PSAD > 0.15) and applying a standardized national QA framework. The study therefore aims to generate definitive evidence for or against omission of SB in MRI-positive men within a German healthcare setting.

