#### Sample size

The sample size is derived from the following expected PI-RADS distribution (own institutional data and PRECISION trial data [8, 23]): 25% PI-RADS 1–2, 25% PI-RADS 3 (15% PSAD ≤ 0.15 and 10% PSAD > 0.15), 30% PI-RADS 4, and 20% PI-RADS 5. Thus, the prevalence of PI-RADS 4/5 and PI-RADS 3 PSAD > 0.15 is estimated at 60%. The estimated prevalence of csPCa in this cohort is 50%, and the detection of low-grade PCa (ISUP 1) is expected to be 15%.

Based on prior evidence, targeted biopsy alone is expected to reduce ISUP 1 detection by at least 40% [7], and SB adds approximately 5% absolute incremental csPCa detection according to randomized trials and a Cochrane meta-analysis [9, 10, 13, 14]. Non-inferiority of TB alone compared with TB + SB will be evaluated by testing H0: Δ0 = πTB − πSB + TB ≤ − δNI, with a non-inferiority margin of δNI = 13%. The non-inferiority margin of 13% was chosen based on prior evidence demonstrating an approximate 4–5% incremental detection of clinically significant prostate cancer with systematic biopsy, allowing for a conservative margin that maintains clinical relevance. Assuming πSB + TB = 50% and a true difference of Δ = − 5%, 477 patients per arm ensure 80% power at one-sided α = 0.05.

Superiority in avoiding ISUP 1 diagnoses will be tested under H0: πTB/πSB + TB ≥ 1. With πSB + TB = 15% and a true reduction ratio to 60%, a sample size of 460 patients per arm ensures 88% power at *α* = 0.05.

Therefore, 1590 analyzable patients are required (2 × 477/0.6 = 1590), and accounting for 20% dropout, approximately 1908 must be allocated within 3 years.

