## Statistical methods

### Statistical methods for primary and secondary outcomes {20a}

The primary analysis will compare the detection proportion of clinically significant prostate cancer (csPCa; ISUP ≥ 2) between Arm A (TB only) and Arm B (TB + SB) using a non-inferiority framework. Non-inferiority for csPCa detection will be assessed based on the absolute difference in detection proportions (π_TB − π_TB + SB), evaluated using the likelihood score test by Gart and Nam for binomial parameters at a one-sided α level of 0.05. The non-inferiority margin is δ = 13%. Superiority testing for the secondary co-primary endpoint (detection of clinically insignificant PCa, ISUP 1) will be evaluated based on the ratio of detection proportions (π_TB/π_TB + SB) using a one-sided α level of 0.05. All hypothesis tests apply a fixed global significance level of *α* = 0.05.

Secondary outcomes—including biopsy-related complications, biopsy avoidance, diagnostic performance measures, and biopsy approach comparisons—are defined in the Outcomes section according to domain, measurement, metric, method of aggregation, and timepoint. Biopsy-related complications will be summarized as proportions by study arm at 30 days post-procedure. Biopsy avoidance will be reported as the proportion of participants not undergoing biopsy following mpMRI triage at screening. Diagnostic performance outcomes (e.g., DRE, bpMRI vs mpMRI) will be evaluated using standard accuracy measures (e.g., sensitivity, specificity) where applicable.

All detection outcomes are defined as proportions (number of participants with the outcome divided by the number of participants undergoing biopsy in the respective arm). Secondary outcomes will be analyzed descriptively and, where appropriate, using inferential statistical methods.

Patient-reported outcomes (EPIC-26, EORTC-QLQ-C30, VAS) will be analyzed using mixed models for repeated measures (MMRM), including treatment arm, timepoint, and baseline values as covariates.

A detailed statistical analysis plan (SAP) will be finalized and archived prior to database lock and prior to any unblinded analyses.

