### Methods for additional analyses (e.g., subgroup analyses) {20b}

Pre-specified subgroup analyses will explore whether the effect of targeted biopsy alone versus combined biopsy on the detection proportion of clinically significant prostate cancer (csPCa; ISUP ≥ 2) varies across clinically relevant strata, assessed at index biopsy.

Planned subgroup analyses include:PI-RADS category: PI-RADS 4 vs PI-RADS 5PSA density (PSAD): ≤ 0.15 vs > 0.15–0.20 vs > 0.20Biopsy approach: transrectal vs transperinealProstate volume: < 60 ml vs 60–100 ml vs > 100 mlAge categories: 50–60, 61–70, 71–75 yearsNumber of MRI lesions: single index lesion vs multiple lesionsMRI quality: PI-QUAL 2 vs PI-QUAL 3Follow-up imaging outcome: stable vs up- or downgraded PI-RADS at 12 monthsHistopathology outcome: ISUP 1 only vs no cancer on initial biopsy

Interaction terms will be evaluated using logistic regression models to assess effect modification on the primary endpoint. All subgroup analyses will be exploratory, hypothesis-generating, and interpreted descriptively without correction for multiplicity.

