## Discussion

The PRIMA study is designed to resolve a central question in modern prostate diagnostics: is systematic biopsy still required for biopsy-naïve men in the era of high-quality mpMRI and fusion-guided TB? Current evidence remains mixed. Trials such as PRECISION [8], MRI-FIRST [9], and 4-M [10] confirmed that mpMRI-guided TB achieves high csPCa detection, but residual incremental detection from SB remains. Screening trials like STHLM3-MRI [11] and Göteborg-2 [12] further emphasized that omitting SB reduces overdetection but carries a marginal risk of missing csPCa. Thus, guidelines differ internationally, and a definitive, high-quality randomized trial within a controlled QA environment is urgently needed. Compared to prior studies, PRIMA features several distinguishing elements. First, strict preselection limits biopsy to men with PI-RADS 4/5 or PI-RADS 3 with PSAD > 0.15, consistent with German guideline recommendations [15, 24]. This enriched population minimizes unnecessary biopsies while maintaining csPCa yield. Second, mpMRI is mandatory rather than optional or replaced by bpMRI, ensuring maximal lesion characterization, especially in younger cohorts where imaging interpretation is more challenging [18, 19]. Third, uniform QA through PI-QUAL and operator certification standardizes both imaging and biopsy performance across all sites. Finally, inclusion of PROs allows holistic assessment of diagnostic burden, patient satisfaction, and complication profiles. The study also integrates advanced research objectives such as AI and radiomics model validation. By linking imaging features, histopathology, and PRO data, PRIMA aims to establish predictive algorithms for csPCa and quality-of-life outcomes, providing a platform for future personalized diagnostics. Expected benefits include reduced biopsy numbers, lower infection rates, and fewer ISUP 1 detections—leading to substantial health-economic savings [2, 3, 7]. Conversely, if SB omission compromises csPCa detection, results will clarify which subgroups (e.g., age, prostate volume, PI-RADS 3) still benefit from combined sampling. The standardized design and large sample will support guideline updates, reimbursement decisions, and possible nationwide implementation of MRI-only pathways if non-inferiority is demonstrated. Lastly, the PRIMA trial will further assess under which conditions and to what extent MRI in-bore biopsy constitutes a valid and safe approach within a targeted biopsy-only paradigm [25–28]. Limitations include potential selection bias toward academic centers with strong MRI expertise and limited generalizability to less-specialized institutions. Nevertheless, PRIMA’s rigorous QA, centralized monitoring, and defined endpoints ensure validity and reproducibility. Its findings will directly influence diagnostic policy, reduce overtreatment, and optimize early detection of clinically meaningful prostate cancer in Germany.

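### Effect modification by age, prostate volume and PSA density is assessed only across three bands, which costs a modest amount of already low interaction power

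*Protocol article*

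**What the plan says.** The section on additional analyses ({20b}) asks whether the effect of TB alone versus TB + SB on detection of clinically significant cancer "varies across clinically relevant strata, assessed at index biopsy". Three of the listed factors are continuous measures cut into three:

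- age: 50–60, 61–70, 71–75 years;
- prostate volume: < 60, 60–100, > 100 ml;
- PSA density: ≤ 0.15, > 0.15–0.20, > 0.20.

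It then says: "Interaction terms will be evaluated using logistic regression models to assess effect modification on the primary endpoint". No continuous form is mentioned. The status of the analyses is clear: "All subgroup analyses will be exploratory, hypothesis-generating, and interpreted descriptively without correction for multiplicity".

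The Discussion gives them a purpose. If leaving out SB costs detection, "results will clarify which subgroups (e.g., age, prostate volume, PI-RADS 3) still benefit from combined sampling". The Background refers to findings in a younger cohort, "suggesting that MRI interpretation and tumor biology may differ with age".

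**The concern.** If the added yield of SB changes gradually with age, gland size or PSA density, three bands are an inefficient way to detect it. Men at opposite ends of a band are treated as alike, and the test needs two interaction coefficients where one would do. Of the cut-points, only PSA density 0.15 is tied to anything else in the article, namely the randomization rule for PI-RADS 3.

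The trial is sized for the overall comparison, so interaction tests start with little power. Losing more raises the chance that real effect modification is missed. A small top volume band would also give a very noisy estimate. At stake is how well the trial can answer the Discussion's question about who still benefits from SB. The primary non-inferiority result is not at stake.

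**Working it through.** **1. The plan's own figure.** Inputs from the Sample size section: "Assuming πSB + TB = 50% and a true difference of Δ = − 5%, 477 patients per arm ensure 80% power at one-sided α = 0.05", with a 13-point margin. The test is the Gart–Nam score test ({20a}). The rates that satisfy the margin and best fit 45% and 50% are about 41.05% and 54.05%.

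- SD under the null: √(0.4105×0.5895 + 0.5405×0.4595) ≈ 0.700
- SD under the alternative: √(0.45×0.55 + 0.50×0.50) ≈ 0.705
- n = [(1.645×0.700 + 0.842×0.705)/(0.13 − 0.05)]² ≈ 476.02, rounded up to 477 per arm

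The figure reproduces (unpooled variance gives 481). So 2 × 477 = 954 men enter the interaction tests. The article states no power for any of these tests.

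**2. Set-up for the interaction tests.**

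- From the article: n = 954, 1:1 allocation, 50% detection with TB + SB, 45% with TB alone, so a mean log odds ratio of log(0.45/0.55) = −0.20.
- Assumed, because the article gives none: two-sided 0.05; a detection rate with TB + SB that does not vary with the measure; age truncated normal (mean 63–65, SD 6–7) or uniform on 50–75; volume log-normal (median 45–55 ml, log-SD 0.45); PSA density log-normal (median 0.15–0.20, log-SD 0.55).
- Effect of TB alone at standardized value z: log odds ratio = min(0, a + slope × z), with a set so that the mean stays at −0.20. The cap at zero means that TB alone never outperforms TB + SB.
- Power: λ = 2 × (expected log-likelihood with the interaction minus that without it). Power = P(noncentral χ² with parameter λ > c), where c = 3.84 for the continuous term (1 df) and 5.99 for three bands (2 df).

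**3. Results with the cap.** SB adds more at low values of the measure.

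| Measure | Slope per SD | Continuous | Three bands | Loss (points) |
|---|---|---|---|---|
| Age, normal 65/6 | 0.10 | 12.0% | 8.6% | 3.4 |
| | 0.20 | 25.6% | 16.0% | 9.6 |
| | 0.30 | 35.9% | 24.2% | 11.7 |
| Log volume, median 55 ml | 0.10 | 11.7% | 8.2% | 3.5 |
| | 0.30 | 33.6% | 18.4% | 15.2 |
| Log PSA density, median 0.15 | 0.10 | 11.7% | 8.3% | 3.4 |
| | 0.30 | 33.6% | 20.9% | 12.7 |

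Across the assumed distributions the loss is about 3–12 points for age, 4–21 for volume and 3–13 for PSA density. The upper end for volume (21 to 22, depending on how far the tails are carried) comes from a median of 45 ml. There about 74% of men fall below 60 ml, so most of the gradient lies inside one band. If SB instead adds more in larger glands, the volume loss is about 3–10 points.

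**4. Without the cap.** The same calculation with a straight line gives larger losses. For age (normal 65/6) at slope 0.30, power is 62.7% against 41.8%, a loss of 20.9 points. But that line makes TB alone better than TB + SB in about 27% of men. At slope 0.20 the share is 17%.

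**5. When the bands win.** With an effect of 0.4 log odds per SD of the effect function and age normal 65/7, a step at 71 years gives the banded test about 73% and a linear term 42%. A U-shape gives 46% and 8%.

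**The case against.** The strongest reply has four parts.

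- **The degrees of freedom are inferred.** The article does not say how age, volume or PSA density enter the logistic model, and an analysis plan that is not shown may add a continuous form. This stands as a caution. But effect modification is framed across strata, the strata are listed as bands, and the interaction sentence follows. Banding is the form the text states. Scoring the bands as a 1-df trend would reduce the loss, but no such scoring is mentioned.
- **The analyses are exploratory.** No margin, sample size or decision rests on an interaction p-value. This stands and limits the point to a minor improvement.
- **Power is low under either coding**, so a non-significant result says little in any case. This is true in the scenarios above.
- **The gradient is not established.** The Background says only that interpretation and biology may differ with age, citing a younger screening cohort. It states no linear trend within 50–75 years. A step or U-shape would favour the bands.

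A reader might infer that banding costs 20 points of power or more for age. The design does not support that. Arm B receives the targeted biopsy plus SB, so leaving SB out should not raise expected detection in any group of men. Age losses of that size appear only when TB alone outperforms TB + SB in a sizeable share of men.

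**Conclusion.** The point holds as a modest loss of efficiency in exploratory analyses. Under a monotone interaction in which TB alone never beats TB + SB, with slopes of 0.10–0.30 log odds per SD, three bands tested on 2 df lose about 3–12 points of power for age, 4–21 for volume and 3–13 for PSA density. Continuous terms reach only about 12–36% power in these scenarios. At the weakest slope the loss is 3–4 points.

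The size depends on assumed distributions, a flat detection rate with TB + SB, and the shape of the effect. It should be read as a range. The cut-points are not errors, and nothing here touches the non-inferiority or ISUP 1 conclusions. Nor would the change turn these tests into well-powered ones. It would make better use of data already collected for the question raised in the Discussion.

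**What to change.** In section {20b}, or in the analysis plan before database lock, state that the arm interactions with age, log prostate volume and log PSA density are tested as continuous terms (one linear interaction each), with a restricted cubic spline to check shape. Plot the estimated arm difference in detection against each measure with its confidence band. Keep the listed categories for descriptive tables and forest plots, and keep the exploratory label.

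The cost is a sentence or two of wording and a little more analysis, with no new data. The downside is that a linear term can miss a step or a non-monotone pattern. The spline and the retained bands cover that. When PSA density is interpreted, note that randomized men at or below 0.15 are all PI-RADS 4–5 by the entry rule, so that comparison is mixed with PI-RADS category under either coding.

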## Assignment of interventions: allocation

### Sequence generation {16a}

Participants will be randomized in a 1:1 allocation ratio to either Arm A (targeted biopsy only) or Arm B (targeted + systematic biopsy). Randomization will use computer-generated permuted blocks of variable size and will be stratified by study center to ensure balance across recruitment sites.

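### The csPCa effect is defined as an absolute difference, but its variation across subgroups is to be assessed with logistic interactions, which compare odds ratios and can order strata differently

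*Protocol article*

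**What the plan says.** Statistical methods {20a} sets the scale of the primary effect: "Non-inferiority for csPCa detection will be assessed based on the absolute difference in detection proportions", tested against a margin of 13 percentage points. The Sample size section plans on the same scale. It takes 50% detection with TB + SB, holds that "SB adds approximately 5% absolute incremental csPCa detection", and concludes that "477 patients per arm ensure 80% power at one-sided α = 0.05".

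Section {20b} then poses the subgroup question in terms of the detection proportion: does the effect of TB alone against TB + SB on it differ between strata? The planned strata include PI-RADS 4 against 5, PSA density, prostate volume and age. The one method given is: "Interaction terms will be evaluated using logistic regression models to assess effect modification on the primary endpoint". The same section labels all subgroup analyses exploratory, to be read descriptively and without multiplicity correction.

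The Discussion gives the results a purpose: "if SB omission compromises csPCa detection, results will clarify which subgroups (e.g., age, prostate volume, PI-RADS 3) still benefit from combined sampling".

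**The concern.** An interaction term in a logistic model tests whether odds ratios are equal across strata. The question in {20b}, and the use described in the Discussion, concern how many csPCa diagnoses are lost per 100 men in each stratum. The two coincide only when strata have similar csPCa rates. PI-RADS category and PSA density are of interest largely because cancer risk is expected to differ across them.

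Three things can follow. Strata with different absolute losses can show no logistic interaction. Strata with the same absolute loss can show different odds ratios. The stratum with the more extreme odds ratio can be the one that loses fewer diagnoses. Since the subgroup results are meant to indicate who still benefits from combined sampling, the estimate that is displayed matters even when nothing is formally tested.

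**Working it through.** **1. The plan's own figure is on the absolute scale.** Inputs from the Sample size section: 50% against 45%, margin 13 points, one-sided α 0.05, power 80%. The distance from the margin is 13 − 5 = 8 points.
- Unpooled normal approximation: n = (1.645 + 0.842)² × (0.50×0.50 + 0.45×0.55) / 0.08² = 481 per arm.
- Score version, with rates constrained to differ by 13 points under the null (0.4105 and 0.5405): n = [(1.645×0.7003 + 0.842×0.7053)/0.08]² = 476.02, rounded up to 477. Power at 477 is 80.1%.

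The stated 477 therefore reproduces as a risk-difference calculation.

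**2. Stratum sizes and assumed rates.** The Sample size section expects PI-RADS 3 with PSAD > 0.15, PI-RADS 4 and PI-RADS 5 in the ratio 10:30:20. Of 477 per arm this gives 477×30/60 = 238.5 men in PI-RADS 4 and 477×20/60 = 159 in PI-RADS 5. The document gives no csPCa rate by category. I assume TB + SB rates that reproduce its 50%:
- 10/40/85%: (10×10 + 30×40 + 20×85)/60 = 3000/60 = 50%.
- 20/40/80%: (200 + 1200 + 1600)/60 = 50%.
- 15/45/75%: (150 + 1350 + 1500)/60 = 50%.

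**3. Misplaced.** Take 10/40/85% with losses of 7 points in PI-RADS 4 and 5 points in PI-RADS 5.
- PI-RADS 4, 40% to 33%: OR = (0.33/0.67)/(0.40/0.60) = 0.739.
- PI-RADS 5, 85% to 80%: OR = (0.80/0.20)/(0.85/0.15) = 0.706.

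The odds ratio marks PI-RADS 5 as worse although PI-RADS 4 loses more. This lies near the planned effect: 7×30/60 + 5×20/60 = 5.2 points overall before any PI-RADS 3 loss.

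**4. Hidden.** The planned 50% to 45% is an OR of (0.45/0.55)/(0.50/0.50) = 0.818. Applying it in both strata makes the logistic interaction exactly zero. The TB rate is o/(1+o), with o = 0.818 × p/(1−p).
- At 40%: o = 0.5455, rate 35.3%, loss 4.7 points.
- At 85%: o = 4.636, rate 82.3%, loss 2.7 points.

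**5. Range over the assumed rates (PI-RADS 4 / PI-RADS 5).**

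| TB + SB rates | Losses at common OR 0.818 | ORs at a uniform 5-point loss | ORs at losses of 7 and 5 points |
|---|---|---|---|
| 40% / 85% | 4.7 / 2.7 | 0.81 / 0.71 | 0.74 / 0.71 |
| 40% / 80% | 4.7 / 3.4 | 0.81 / 0.75 | 0.74 / 0.75 |
| 45% / 75% | 4.9 / 3.9 | 0.81 / 0.78 | 0.75 / 0.78 |

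For 7 and 5 points lost, only the widest spread reverses the order. Between 30% and 70%, a common OR of 0.818 means losses of 4.0 to 5.0 points, so the scales nearly agree.

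**6. Precision.** For the scenario in step 3, the difference of risk differences is 2 points. Its standard error is √[(0.40×0.60 + 0.33×0.67)/238.5 + (0.85×0.15 + 0.80×0.20)/159] = √0.00374 = 6.1 points. The log-odds interaction is ln 0.739 − ln 0.706 = 0.046, with a standard error of about 0.35. Neither can be detected. On the risk-difference scale itself the estimate would point to the wrong stratum with probability Φ(−2/6.1), about 37%.

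**The case against.** Logistic interaction is a common choice for a binary endpoint, the analyses are expressly exploratory, and no decision rule depends on them. At the planned effect, the hidden gap between PI-RADS 4 and 5 is about 1 to 2 points against a standard error of about 6. The document does not rule out showing proportions or differences by stratum, and an analysis plan could add them. All of this stands and limits the size of the point. It does not remove it, because {20b} names a method that answers a different question from the one it poses.

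Stronger readings are tempting but unsupported:
- A reader might infer that the odds ratio would name the wrong stratum in a large share of trials, using a steeper contrast such as 45% and 85% in PI-RADS 4 and 5. With the plan's mix and 50% overall, PI-RADS 3 would then need (3000 − 1350 − 1700)/10 = −5%, which is impossible. Much of any disagreement rate would also be sampling noise, as the 37% in the working shows.
- A reader might use PI-RADS 3 to widen the contrast. The Discussion mentions PI-RADS 3, but the listed comparison is PI-RADS 4 against 5.
- A reader might infer that no absolute subgroup results will be shown. The text names none, but it does not exclude them.
- A reader might want each subgroup interval judged against 13 points. That margin was set for the whole randomized cohort. With about 80 men per arm in PI-RADS 3 and a rate near 20%, a 90% interval has a half-width of about 10 points, so a 5-point loss would cross −13.

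**Conclusion.** The mismatch is real and stated in the text: the effect is defined and sized as an absolute difference, the subgroup question concerns the same quantity, and the only named method works on odds ratios. It is a minor point. Under rates consistent with the plan, the odds ratio can mark the stratum with the smaller absolute loss as worse (0.71 for 5 points, 0.74 for 7 points), and a null logistic interaction can cover losses of 4.7 and 2.7 points. Both results rest on assumed rates of 10/40/85%. With a narrower spread the hidden gap shrinks to about 1 point and the reversal for 7 and 5 points disappears. Changing the scale does not make the interaction tests well powered; it makes the displayed estimates answer the question asked. The primary analysis and the 477 per arm are unaffected.

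**What to change.** In {20b}, state that:
- for each baseline subgroup, the difference in csPCa detection (TB minus TB + SB) is reported with a confidence interval;
- effect modification is described as a difference of risk differences, for example by standardising predictions from the logistic model already planned;
- the odds-ratio interaction is kept as a supplementary result;
- these results are read descriptively, with no subgroup non-inferiority verdict against the 13-point margin.

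The cost is a sentence or two of wording and a little extra analysis, with no new patients or data. Intervals will be wide in small strata. Standardising the logistic model avoids the convergence failures that an identity-link model may meet there. According to Trial status, no participants had been enrolled at submission, and {20a} says the analysis plan is still to be finalised, so the change can be made before any data are seen.

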#### Secondary outcomes

Patient-reported outcomes (EPIC-26, EORTC-QLQ-C30, VAS)

Measured using validated questionnaires (metric: continuous scores), analyzed as mean changes over time and between groups (aggregation: mean differences), assessed at baseline, 30 days, and 12 months.Biopsy-related complications

Defined as adverse events within 30 days post-biopsy (measure: clinical assessment; metric: categorical/binary), summarized as proportions by study arm, assessed at 30 days post-procedure.Biopsy avoidance due to mpMRI triage

Defined as the proportion of participants not undergoing biopsy due to non-suspicious mpMRI findings (PI-RADS 1–2 or PI-RADS 3 with PSAD ≤ 0.15), reported as proportion, assessed at screening.Diagnostic performance of DRE

Defined as the association between DRE findings and biopsy outcomes (metric: sensitivity, specificity), analyzed cross-sectionally at baseline and biopsy.Biopsy approach (transrectal vs. transperineal)

Compared in terms of pain (VAS score) and infection rates (binary), summarized as mean differences and proportions, assessed within 30 days post-biopsy.MR in-bore biopsy yield

Defined as detection of csPCa in participants undergoing MR in-bore biopsy after negative or ISUP 1 results (metric: binary), reported as proportion, assessed within 3 months post-biopsy.Detection of higher-grade cancer (ISUP ≥ 3)

Defined as presence of ISUP ≥ 3 cancer on histopathology (metric: binary), reported as proportion, assessed at index biopsy.Comparison of bpMRI vs mpMRI

Retrospective comparison of detection performance (metric: paired binary outcomes), analyzed using constrained maximum likelihood methods, assessed at baseline imaging.Change in PI-RADS score

Defined as change in PI-RADS category between baseline and follow-up MRI (metric: ordinal change), reported as proportions of up- or downgrading, assessed at 12 months.Index-lesion-only analysis

Detection of csPCa based on index lesion targeting only (metric: binary), reported as proportion, assessed at index biopsy.AI and radiomics validation

Diagnostic performance of AI-based models (metric: AUC, sensitivity, specificity), analyzed retrospectively, assessed using baseline imaging and biopsy outcomes.

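### The Discussion expects results to show which men still need systematic biopsy, but the only subgroup method named, a between-arm interaction test, resolves differences of about 18 to 24 points; a stratified systematic-only yield in Arm B should be added beside it.

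*Protocol article*

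**What the plan says.** The section on additional analyses {20b} asks whether the effect of TB alone versus combined biopsy on csPCa detection differs across listed strata. The method is: "Interaction terms will be evaluated using logistic regression models to assess effect modification on the primary endpoint". The same section calls all subgroup analyses exploratory and descriptive, without multiplicity correction. Its PI-RADS comparison is category 4 versus 5 only.

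The Discussion says that, if leaving out SB compromises csPCa detection, "results will clarify which subgroups (e.g., age, prostate volume, PI-RADS 3) still benefit from combined sampling".

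The Sample size section supplies the planning values: "The estimated prevalence of csPCa in this cohort is 50" percent, "SB adds approximately 5% absolute incremental csPCa detection", and "477 patients per arm ensure 80% power". Under Secondary outcomes there is an index-lesion analysis ("Detection of csPCa based on index lesion targeting only"), but no outcome for csPCa found by systematic cores alone in Arm B, either overall or by stratum. Under the Trial design and Prostate biopsy sections, Arm B men receive both targeted and systematic cores.

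**The concern.** The interaction test compares different men: Arm A with Arm B inside each stratum, and then one stratum with another. With csPCa near 50%, each stratum difference carries the full variance of two independent proportions. The quantity sought, the extra yield of SB, is expected to be only about 5 points.

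Arm B holds more direct information. Among men who have both sets of cores, csPCa on either set minus csPCa on targeted cores is, by identity, the share with csPCa on systematic cores only. That is one proportion near 5%, with about a tenth of the variance. The subgroup section does not use it.

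At stake is the follow-up question the Discussion raises, not the primary conclusion. A flat interaction could be taken to mean that no group needs SB, and a chance finding among nine uncorrected factors to mean that one does. For PI-RADS 3, one of the Discussion's three examples, no PI-RADS contrast is planned at all.

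**Working it through.** **Inputs.** From Sample size: 477 analysable men per arm; csPCa 50% with TB + SB and, at the assumed 5-point loss, 45% with TB; PI-RADS shares of 10 (category 3 with PSAD > 0.15), 30 (category 4) and 20 (category 5) out of the 60% randomised. From Sequence generation: "Participants will be randomized in a 1:1 allocation ratio". Assumed, because the protocol does not state them for these tests: two-sided 5% and 80% power. Also assumed at first: the same csPCa and SB-only rates in every stratum.

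**The plan's own figure.** For a 13-point margin, a true difference of −5 points and one-sided 0.05, the unpooled formula gives n = (1.645 + 0.842)² × (0.45 × 0.55 + 0.50 × 0.50) / 0.08² = 481 per arm. The score version, with variance constrained under the null, gives 476.02, so 477. The stated size is reproduced, so the inputs are read as intended.

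**Stratum sizes per arm.** PI-RADS 3: 477 × 10/60 = 79.5. PI-RADS 4: 477 × 30/60 = 238.5. PI-RADS 5: 477 × 20/60 = 159. PI-RADS 4/5 together: 397.5.

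**Formulas**, for strata with n₁ and n₂ men per arm:
- Interaction (difference of risk differences): SE = √[0.4975 × (1/n₁ + 1/n₂)], where 0.4975 = 0.45 × 0.55 + 0.50 × 0.50.
- SB-only csPCa within Arm B at rate s: SE = √[s(1 − s) × (1/n₁ + 1/n₂)]; at s = 0.05, s(1 − s) = 0.0475.
- Detectable difference = (1.960 + 0.842) × SE.

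| Contrast | Interaction: SE, detectable | Arm B SB-only at 5%: SE, detectable |
|---|---|---|
| Two equal halves (illustrative) | 6.5, 18.1 points | 2.0, 5.6 points |
| PI-RADS 4 vs 5 (planned) | 7.2, 20.2 | 2.2, 6.3 |
| PI-RADS 3 vs 4/5 (not listed) | 8.7, 24.3 | 2.7, 7.5 |

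Simulated logistic Wald tests of the interaction gave 80%, 81% and 84% power at 18.1, 20.3 and 24.3 points for these three splits, so the risk-difference approximation is adequate. With one-sided 5% testing the interaction figures are 16.1, 18.0 and 21.5 points.

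**Range of the precision ratio.** √(0.4975/0.0475) = 3.2 at a 5% SB-only rate. It is 4.1 at 3%, 2.4 at 10% and 2.1 at 13%. The last value reads the Background figure ("SB identified 26% additional csPCa compared with TB alone") as about 13 points on a 50% rate, which is an assumption. If csPCa prevalence differs by stratum (assumed: 20% in PI-RADS 3, or 80% in PI-RADS 5), the ratio is about 2.6 to 2.9 and the interaction still needs 18 to 20 points.

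**Unequal SB-only rates.** The 7.5 points in the last row use 5% variance in both strata, which is optimistic if the small stratum has the higher yield. Holding the overall rate at 5%, a 7.5-point gap means 11.25% in PI-RADS 3 and 3.75% in 4/5. The SE is then √(0.1125 × 0.8875/79.5 + 0.0375 × 0.9625/397.5) = 3.7 points, and power is 53%. Reaching 80% takes about 11.3 points (14.4% vs 3.1%). Against 24.3 for the interaction, the gain is 24.3/11.3 ≈ 2.2-fold.

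**The case against.** The strongest reply is that nothing in {20b} is wrong. Treatment-by-subgroup terms are the standard randomised method, low interaction power is usual in a trial sized for its main effect, and the section claims no subgroup power. A reader might infer a failed power claim or an invalid analysis; the text supports neither. The Discussion sentence is also conditional on SB omission doing harm, and it does not say which results will provide the clarification. The analysis plan, not shown here, may add a table of this kind. All of that stands. What remains is the gap between what the Discussion expects and what the one named method can resolve.

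The Discussion's condition also lowers the gain: if omission does harm, the SB-only rate is probably above 5%, where the ratio falls towards 2. Of the three contrasts above, only PI-RADS 4 versus 5 is both planned and has a documented split. Shares for the age and volume strata are not given.

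It is tempting to go further and make the Arm B proportion the main subgroup estimate. The documents do not support that. It is a non-randomised measure from operators who cannot be blinded and who know that systematic cores will follow, so targeting in Arm B may differ from Arm A. Comparing targeted-core csPCa between arms tests this only coarsely. The 95% half-width is 1.96 × √(2 × 0.45 × 0.55/477) = 6.3 points overall and, with 79.5 per arm, 15.5 points in PI-RADS 3. Neither excludes a targeting difference as large as the expected SB yield.

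Nor can the data be called already collected. Separate recording of targeted and systematic histology is implied by the index-lesion outcome but not stated, and nobody had been enrolled at submission.

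**Conclusion.** The point holds as a mismatch that is cheap to repair, not as an error in the primary analysis or a breach of a stated power claim. Under the plan's own inputs, with two-sided 5% and 80% power assumed, the interaction test separates strata only when the SB effect differs by about 18 points (even split) or 20 (PI-RADS 4 vs 5). It would need about 24 for PI-RADS 3 versus 4/5. These are roughly 3.6 to 4.9 times the whole expected SB yield of 5 points.

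The Arm B systematic-only proportion is about two to four times as precise over SB-only rates of 13% down to 3%, and about 2.2-fold better in detectable difference when a small stratum has the higher yield. That justifies adding it as a supplement. It does not justify demoting the randomised contrast.

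**What to change.** - In {20b}, keep the interaction analyses. Add, as a pre-specified supplementary analysis, the proportion of Arm B men with csPCa on systematic cores only, by baseline stratum with 95% CI.
- Beside it, report csPCa on targeted cores in each arm, stating that this checks equal targeting only to about ±6 points overall and ±15 in PI-RADS 3.
- Confirm before enrolment that the eCRF records targeted and systematic core histology separately.
- Add PI-RADS 3 to the PI-RADS strata so that {20b} and the Discussion agree.
- Reword the Discussion sentence to what exploratory estimates can show.

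The cost is a few lines of text, one table and a check of the eCRF. The price in inference is that the added estimate rests on operators targeting equally well when SB follows, and this should be stated wherever it is reported.
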